## Design

The RHYTHMIC study is a multicenter, prospective randomized controlled trial comparing AV node ablation and AF ablation in patients with CRT and suboptimal (<95%) biventricular pacing secondary to AF. The study conforms to the Declaration of Helsinki, and ethical approval has been granted by the Health Research Authorities and London – Chelsea Research Ethics Committee (21/LO/0116). The study is funded by the European Research Council (864055) and British Heart Foundation (RG/20/4/34803).

### Trial design

Seventy patients with existing CRT devices (implanted for dyssynchronous heart failure) and suboptimal (<95%) biventricular pacing due to AF will be included in the study. Patients will be randomized to either AV node ablation or AF ablation in a 1:1 ratio and will be followed up at 6 months.

### Eligibility

Inclusion and exclusion criteria are shown in Table 1. Eligible patients identified via cardiology outpatient clinics, pacing clinics, or inpatient wards will be informed about the study and provided with a patient information sheet. After reading the information sheet and after questions have been addressed, eligible patients will provide written informed consent for participation in the study. The protocol and data collection are summarized in Figure 1. Both conventional CRT “responders” and “nonresponders” will be included, as patients may experience a deterioration in biventricular pacing owing to new-onset or worsening AF after the initial assessment of response.

**Table 1 tbl1:** Patient eligibility

Inclusion criteria	Exclusion criteria
Age 18–85 years	Life expectancy <1 year
Ability to provide informed consent to participate and willing to comply with the clinical investigation plan and follow-up schedule	Permanent atrial fibrillation
QRS duration >120 ms on surface ECG, severe left ventricular systolic impairment (EF ≤35%), and clinical symptoms of heart failure despite optimum medical therapy (NYHA class II–IV) at time of CRT implant or upgrade	Presence of atrial or ventricular thrombus
Successful CRT implant or upgrade including atrial lead	Mechanical aortic valve replacement
Biventricular pacing percentage <95% secondary to atrial fibrillation at least 3 months post implant or upgrade, despite optimal pharmacological rate control	Severe peripheral vascular disease
Clinically indicated for AV node ablation	Female participants who are pregnant, lactating, or planning pregnancy during the course of the study
	LA diameter >6 cm
	Persistent AF duration >3 years
	Participation in other studies with active treatment / investigational arm

AF = atrial fibrillation; AV atrioventricular; CRT = cardiac resynchronization therapy; ECG = electrocardiogram; EF = ejection fraction; LA = left atrial; NYHA = New York Heart Association.

**Figure 1 fig1:**
[figure not shown]
Flow diagram of study protocol. AF = atrial fibrillation; AV = atrioventricular; ECG = electrocardiogram.

### Baseline data collection

At baseline visit the patients will undergo clinical assessment, medication history, electrocardiogram (ECG), 6-minute walk test, Minnesota Living with Heart Failure Questionnaire, blood tests (including serum NT-proBNP), device check, and transthoracic echocardiogram. Cardiac device metrics collected will include AF burden, AF duration, biventricular pacing percentage, and previous ICD therapies. Echocardiographic metrics will include 2-dimensional LV end-diastolic volume, LV end-systolic volume, LV ejection fraction, and left atrial size. After the baseline visit, patients will be randomized 1:1 using dedicated software to either AV node ablation or AF ablation. Randomization will be stratified using the minimization method by heart failure etiology (ischemic or nonischemic) and by AF type (paroxysmal or persistent).

### Ablation procedure

Patients will receive either AV node ablation or AF ablation according to randomization. For patients undergoing AF ablation, either cryoablation or radiofrequency ablation is permitted. They will undergo isolation of all 4 pulmonary veins. Additional lesions considered indicated by the operator are permitted. Patients in AF at the end of the procedure may undergo DC cardioversion to achieve sinus rhythm. Programming of AV delays after restoration of sinus rhythm will be left to the discretion of the operator.

### Follow-up

Patients will undergo transthoracic echocardiogram and ECG 1 week post ablation, to assess acute response. They will then be seen at the 6-month visit, where they will undergo repeat clinical assessment, ECG, 6-minute walk test, blood tests (including serum NT-proBNP), device check, and transthoracic echocardiogram. Patients in the AF ablation arm who have a recurrence of AF during the follow-up period will be permitted 1 re-do ablation, and their follow-up visit will occur 6 months after the second procedure.

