**Results:**

Patients will undergo baseline assessment including transthoracic echocardiography (TTE), device check, blood tests, electrocardiogram (ECG), 6-minute walk test, and symptom questionnaire. They will then undergo either AV node ablation or AF ablation according to their allocated group. Follow-up will occur at 1 week (TTE and ECG) and at 6 months (repeat of baseline investigations). The primary endpoint will be change in left ventricular ejection fraction on TTE.

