### Sample size justification

Previous comparisons between AV node ablation and AF ablation in patients with AF and heart failure (not indicated for CRT) found a -1% change in LV ejection fraction with AV node ablation compared to 8% with AF ablation.^26^ Measurements of changes in ejection fraction in CRT patients receiving AV node ablation or AF ablation have a variability of 7.1%–10.7%,^25^^,^^28^ giving a maximum variability of 11%. Assuming a normal distribution, a group size of 32 for each arm would achieve 90% power to reject the null hypothesis of equal means, with an alpha value of 0.05 to detect the 9% difference in change in LV ejection fraction using a 2-sided independent *t* test. This sample size will also ensure satisfactory 80% statistical power for detection of 7.5% difference in change in LV ejection fraction. To allow for an approximately 10% drop-out rate we will recruit a total of 70 patients.

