### Statistical analysis

Changes in all cardiac metrics between arms will be compared using *t* tests for independent samples. An intention-to-treat analysis will be performed for the primary and secondary endpoints. Subgroup analyses will be performed for important covariates, including heart failure etiology, sex, age, paroxysmal vs persistent AF, and duration of AF. Subsequently, prediction of outcomes will be performed using regression analyses, considering potential confounders and/or mediators. This procedure will have 2 steps. First, we will conduct exploratory analyses through the use of univariate models and graphical checks of pattern between each candidate predictor and outcome variable. On the basis of these results, and after checking that linearity assumptions are correct, we will examine multivariable associations, taking account of potential confounding factors. Predictors in univariate analysis with *P* < .10 will be further tested in a prespecified multivariable regression model. Predictors will be entered into the model in groups determined by time ordering and/or their clinical relevancy. *P* < .05 will be considered statistically significant.

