Any additional clinical benefit for AF ablation over AV node ablation will need to be carefully balanced against the risk of complications, recurrence rate, and need for repeat procedures. AF ablation is a longer and more invasive procedure than AV node ablation, requiring transseptal puncture and, often, transesophageal echocardiography and general anesthesia. AF ablation carries a 2%–3% risk of potentially life-threatening complications,^34^^,^^35^ while complication rates for AV node ablation are comparatively lower.^36^ In the CASTLE-AF study, repeat ablations were performed in 24.5% of patients assigned to AF ablation during the study period, with an overall recurrence rate of 50% at 60-month follow-up.^27^ It is therefore likely that a significant proportion of heart failure patients with CRT who undergo AF ablation will require multiple procedures, and may ultimately require AV node ablation owing to AF recurrence. To justify the increased risk to the patient, along with increased time and financial burden on healthcare systems, the clinical benefits for AF ablation would need to be clear and substantial. Although the cost-effectiveness of AF ablation has been debated, a recent analysis estimated a favorable incremental cost-effectiveness ratio for patients with AF and heart failure of £6438 per quality-adjusted life year within the UK National Health Service.^37^ The cost-effectiveness of AV node ablation for patients with existing CRT devices is not well studied, and results data from the RHYTHMIC study will allow assessment of this important factor, along with comparison with AF ablation.

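### A re-do ablation resets the follow-up clock in the AF ablation arm only, so the primary LVEF change is read at different times in the two arms

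*Protocol article*

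**What the plan says.** The Trial design section gives the general rule: "Patients will be randomized to either AV node ablation or AF ablation in a 1:1 ratio and will be followed up at 6 months". The Follow-up section then makes an exception for one group, "Patients in the AF ablation arm who have a recurrence of AF during the follow-up period". These patients "will be permitted 1 re-do ablation, and their follow-up visit will occur 6 months after the second procedure". The shown text has no corresponding extension for the AV node ablation arm.

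The visit that moves is the one with the final echocardiogram. According to the Abstract, "The primary endpoint will be change in left ventricular ejection fraction on TTE". The Objectives section dates most of the secondary endpoints at 6 months. It also plans a subanalysis that splits the AF ablation arm by rhythm at 6 months and compares both parts with the AV node ablation arm.

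On analysis, the Statistical analysis section says "An intention-to-treat analysis will be performed for the primary and secondary endpoints". The between-arm comparison is an independent-samples t test ("Changes in all cardiac metrics between arms will be compared using" such tests), with no stated term for time of assessment.

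**The concern.** When the primary endpoint is measured should not depend on how the patient has done since randomization, and least of all in one arm only. Here AF recurrence followed by a re-do moves the reading later in the AF ablation arm. Intention to treat keeps each patient in the allocated group but does not equalize the time at which the groups are read. The arm difference therefore combines the effect of the strategies with a difference in elapsed time for the re-treated patients.

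Two further results are affected:

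- **Rhythm subanalysis.** Rhythm at 6 months no longer refers to one time point. For some patients it is 6 months after a single procedure, for others 6 months after a second. The Objectives and Discussion rely on this subanalysis to interpret a null primary result.
- **Event endpoints.** Ventricular arrhythmias and inappropriate ICD shocks, if counted up to the final visit, would be collected over a longer period in re-do patients.

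**Working it through.** **The plan's own figure.** Inputs from the Sample size justification: difference 9 points (−1% "change in LV ejection fraction with AV node ablation compared to 8% with AF ablation"), SD 11, two-sided alpha 0.05, power 90%. The normal approximation is n = 2(1.96 + 1.2816)² × 11² / 9² = 31.4, so 32 per arm, as stated. The exact t calculation gives 33, with 89.6% power at 32. The figure is not in dispute. The standard error of the arm difference is 11 × √(2/32) = 2.75 points.

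**Time of reading.** A re-do at month m after the first procedure puts the final visit at month m + 6. For m between 0 and 6 this is month 6 to month 12, against month 6 for AV node ablation patients.

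**How many patients.** The document does not predict a re-do rate for this trial. The Discussion reports that in a cited heart failure trial "repeat ablations were performed in 24.5% of patients assigned to AF ablation during the study period". I take 24.5% as a high value and 10% as an assumed lower one. With 32 to 35 patients in the arm:

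- 24.5%: 0.245 × 32 = 7.8 to 0.245 × 35 = 8.6 patients
- 10%: 0.10 × 32 = 3.2 to 0.10 × 35 = 3.5 patients

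**Effect on the arm difference.** Let r be the share with a re-do and g the extra LVEF gain at the moved visit compared with a reading at 6 months in the same patients. The AF-arm mean shifts by r × g. The document gives no value for g, so 2 to 9 points is an assumption. The last column is the chance that the two-sided t test rejects (32 per arm, SD 11) when the arms do not differ at a fixed 6 months.

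| r | g (points) | Shift r × g (points) | Rejection rate |
|---|---|---|---|
| 10% | 2 | 0.20 | 5.1% |
| 10% | 4 | 0.40 | 5.2% |
| 10% | 6 | 0.60 | 5.5% |
| 10% | 9 | 0.90 | 6.2% |
| 24.5% | 2 | 0.49 | 5.4% |
| 24.5% | 4 | 0.98 | 6.4% |
| 24.5% | 6 | 1.47 | 8.2% |
| 24.5% | 9 | 2.21 | 12.4% |

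As a share of the 9-point design difference, the shift runs from 0.2/9 = 2% to 2.21/9 = 25%. The SD is held at 11. Mixing shifted and unshifted patients would widen the AF-arm SD a little (at r = 24.5% and g = 9, √(121 + 0.245 × 0.755 × 81) = 11.7), so the largest rejection rates are slightly high.

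**Event exposure.** If events are counted to the final visit, a re-do patient contributes at most 12/6 = 2 times the planned exposure. If r = 24.5% and every re-do fell at month 6, mean AF-arm exposure would be 0.755 × 6 + 0.245 × 12 = 7.5 months against 6. This is an upper case.

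**With a common assessment time** the shift due to timing is zero, the test keeps its nominal 5% in this respect, and the sample size is unchanged.

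**The case against.** The strongest case for the rule is that re-do ablation belongs to the AF ablation strategy, and that every patient should have the same 6 months of recovery after the last procedure. The trial's hypothesis concerns reverse remodeling, which takes time. A reading at a fixed 6 months would catch a patient re-done at month 5 only 1 month later. This stands as a reason to allow re-dos and to collect a later reading. It does not justify making that later reading the primary one in one arm, because a comparison of strategies needs a common clock.

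Other parts of the defence limit the point:

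- **Size of g.** Some of the gain at the moved visit is benefit of the second procedure, which counts as strategy effect, and an early re-do would also contribute at a fixed 6 months. The planning value for AV node ablation, −1%, gives little reason to expect a large gain from time alone. LVEF could even fall over the longer interval.
- **The 24.5% rate.** It covers another trial's whole study period, and the same sentence gives a recurrence figure at 60 months. It is probably high for a window of about 6 months.
- **Scope.** The trial is presented as hypothesis-generating, and even the largest shift above is below one standard error.

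A reader might infer more than the text supports in three places. First, the Follow-up rule might seem to contradict the Trial design section. It is better read as a stated exception to a one-line summary. Second, poor LVEF values might seem to be selectively replaced. The trigger is AF recurrence, not low LVEF; a re-do is permitted and not required; and the article does not say that a reading before the re-do is omitted or discarded. Third, the whole trial might seem tilted towards AF ablation. For event counts, longer exposure would add events to the AF arm and so work against it.

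**Conclusion.** The point holds in a limited form. The document explicitly ties the timing of the primary LVEF reading, and of the 6-month secondary endpoints, to a post-randomization event in the AF ablation arm, and nothing in the stated analysis corrects for this. For LVEF the likely direction favours AF ablation. The size cannot be derived from the document. Under assumed re-do shares of 10% to 24.5% and assumed gains of 2 to 9 points, the calculation gives shifts of about 0.2 to 2.2 points and false-positive rates of about 5.1% to 12.4%. These describe the combined effect of later timing and re-treatment, so the part due to timing alone is smaller. The issue does not invalidate the design or the sample size. It is an inexpensive improvement worth making, preferably before follow-up is complete, because a 6-month echocardiogram that was not done cannot be recovered at analysis.

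**What to change.** In the Follow-up section, schedule the primary LVEF assessment and all 6-month secondary endpoints at 6 months from one common origin in both arms, either randomization or the index procedure, whether or not a re-do has occurred. Keep any assessment 6 months after a re-do as a secondary, descriptive result for the AF ablation arm. Define the rhythm subanalysis at the same common time point. Analyse ventricular arrhythmias and inappropriate shocks per patient-time or over the common window.

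The re-do provision itself and the number of patients do not change. The cost is protocol wording and rescheduling for the re-do patients, about 3 to 9 under the shares assumed above. The downside is that some of them are read soon after the second procedure, before it has had its full effect, or need one optional extra echocardiogram if the later visit is kept.

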### Sample size justification

Previous comparisons between AV node ablation and AF ablation in patients with AF and heart failure (not indicated for CRT) found a -1% change in LV ejection fraction with AV node ablation compared to 8% with AF ablation.^26^ Measurements of changes in ejection fraction in CRT patients receiving AV node ablation or AF ablation have a variability of 7.1%–10.7%,^25^^,^^28^ giving a maximum variability of 11%. Assuming a normal distribution, a group size of 32 for each arm would achieve 90% power to reject the null hypothesis of equal means, with an alpha value of 0.05 to detect the 9% difference in change in LV ejection fraction using a 2-sided independent *t* test. This sample size will also ensure satisfactory 80% statistical power for detection of 7.5% difference in change in LV ejection fraction. To allow for an approximately 10% drop-out rate we will recruit a total of 70 patients.

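### The 80% power claimed for a 7.5-point difference is about 77% at the stated 32 per arm; under the stated test and SD it needs all 70 recruits analysed

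*Protocol article*

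**What the plan says.** All the relevant statements are in the protocol article, under Sample size justification.

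- **Effect.** The planning difference is 9 points, from a previous comparison in heart failure patients without a CRT indication (a change of -1 with AV node ablation against 8 with AF ablation).
- **Variability.** Changes in LVEF in the source studies "have a variability of 7.1%–10.7" percent, which the plan rounds up, "giving a maximum variability of 11" percent.
- **Size and main power.** The plan says that "a group size of 32 for each arm would achieve 90% power to reject the null hypothesis of equal means". The target there is the 9-point difference, tested two-sided at the 5% level by a t test for independent groups.
- **Second power claim.** The next sentence reads: "This sample size will also ensure satisfactory 80% statistical power for detection of 7.5% difference in change in LV ejection fraction".
- **Drop-out.** Only after that does the total appear: "To allow for an approximately 10% drop-out rate we will recruit a total of 70 patients".

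When the second claim is made, the only sample size yet named is 32 per arm.

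**The concern.** The two power statements are offered for the same sample size, SD, alpha and test, so both should follow from the same calculation. At a fixed size, moving from 9 to 7.5 points costs more power than the drop from 90% to 80% allows for. The 80% figure appears to fit the recruited number rather than the evaluable number. If so, one paragraph quotes one power after drop-out and the other before it.

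The 9-point effect comes from patients without a CRT indication, whereas everyone in this trial already has CRT. The 7.5-point sentence is therefore the plan's only statement that a smaller effect could still be found. The Objectives and the Discussion both set out how a null result would be interpreted, and that interpretation should start from the power the design really has.

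**Working it through.** **Inputs** (all from Sample size justification): SD 11; two-sided alpha 0.05; independent-samples t test; 32 per arm; differences of 9 and 7.5 points; 70 recruited; about 10% drop-out. The 1:1 allocation is in Trial design.

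**Formulas.** With n per arm, the standard error of the difference is SE = SD × √(2/n) and the noncentrality is δ = difference / SE. Exact power is the probability that a noncentral t variable with 2n − 2 degrees of freedom and noncentrality δ lies beyond the two-sided 5% critical value. The normal approximation is Φ(δ − 1.96).

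**Step 1: reproduce the main claim.**
- SE = 11 × √(2/32) = 2.75.
- δ = 9 / 2.75 = 3.273.
- Power is 89.6% (t), or Φ(1.313) = 90.5% (normal).
- The normal sample size formula gives n = 2 × (1.96 + 1.2816)² × 11² / 9² = 31.4, so 32 per arm.

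The plan's 32 per arm and 90% are reproduced. This also confirms that SD 11 was the value used.

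**Step 2: the second claim at the same size.**
- δ = 7.5 / 2.75 = 2.727.
- Power is **76.6%** (t), or Φ(0.767) = 77.9% (normal).
- Type II error under the t test is 100 − 76.6 = 23.4%.

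**Step 3: where does 80% hold?** Power at 7.5 points, SD 11, two-sided 0.05:

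| n per arm | t test | normal |
|---|---|---|
| 32 | 76.6% | 77.9% |
| 33 | 77.9% | 79.1% |
| 34 | 79.1% | 80.3% |
| 35 | 80.3% | 81.4% |

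Under the named t test, 35 per arm is the smallest size that reaches 80%, and 2 × 35 = 70 is the full recruitment target.

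**Step 4: detectable difference at 80% power.** At 32 per arm it is 7.83 points (t), or 2.75 × (1.96 + 0.8416) = 7.70 (normal). At 35 per arm it is 7.47 (t).

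**Step 5: other inputs that might explain 80% at 32 per arm.**
- SD 10.7, the unrounded maximum: 78.8% (t), 80.1% (normal). Under the t test the SD would have to be about 10.54.
- One-sided 0.05 with SD 11: 85.4% (t).

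Only SD 10.7 combined with the normal approximation lands on 80%, and that drops both the stated SD and the stated test.

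**Step 6: after the plan's own drop-out.** 70 × 0.9 = 63 evaluable (31 and 32). Power is then 75.9% at 7.5 points and 89.2% at 9 points (t). Retaining the full 64 at exactly 10% loss would need 64 / 0.9 = 71.1 recruits. Conversely, going from 70 to 64 is a loss of 6 / 70 = 8.6%.

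**The case against.** The strongest case on the other side is about weight, not arithmetic. The trial is sized on 90% power at 9 points, and that claim reproduces. The 7.5-point sentence is supplementary and did not determine the 32 or the 70. The gap is 3.4 percentage points of power (2.1 by the normal formula), or about 0.33 LVEF points in detectable difference. That is small beside a source SD ranging from 7.1 to 10.7, already rounded up to 11. A null result would in any case be read from the estimate and its confidence interval, not from a planning figure.

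Much of this stands as a limit on importance. Three details also deserve care:

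- The 35-per-arm requirement is strict. Losing one patient per arm leaves 79.1%, which many would report as about 80%.
- The plan does not say that the second figure was computed on 70. That is the explanation that fits the stated SD and test, but it remains an inference.
- The difference between 63 and 64 is not an error in its own right, because the drop-out is given as approximate and 8.6% is a fair reading of that.

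None of this rescues the sentence. Reading it as referring to 70 patients ignores the drop-out allowed for immediately afterwards. Neither 76.6% nor 77.9% rounds to 80%, whereas the companion figure of 89.6% does round to 90%.

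**Conclusion.** The concern holds. With 32 per arm, SD 11 and a two-sided 0.05 t test, power for a 7.5-point difference is about 77%, not 80%. The difference detectable with 80% power is about 7.8 points. The stated figure is met under those inputs only with 35 analysed per arm, which means no drop-out. The error is modest and confined to the secondary power statement; the primary 90% at 9 points is sound. The result rests on the plan's own SD, alpha and test, with equal arms, and on reading the sample size in that sentence as the 32 per arm just stated. Because the sentence promises a sensitivity to smaller effects that the design does not quite have after its own drop-out allowance, it should be corrected.

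**What to change.** Replace the sentence with one to this effect: with 32 evaluable patients per arm and an SD of 11 points, power is 77% for a 7.5-point difference, and 80% power is reached at 7.8 points. Give both power figures on the number expected after drop-out (63 to 64 patients). If the authors prefer to keep the 80%, they should tie it expressly to 35 analysed per arm with no loss. If a baseline-adjusted analysis is later adopted in place of the t test on change, power should be restated under that model with its assumed correlation; this is optional and not needed for the correction.

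The cost is one sentence and a slightly less favourable figure. Recruitment, endpoint and test are unchanged.
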